### Primary outcome

The primary outcomes are EEG viewing responses, specifically to food images depending on fat and carbohydrate content (HIGH-FAT/LOW-CARB; HIGH-FAT/HIGH-CARB; LOW-FAT/LOW-CARB; LOW-FAT/HIGH-CARB). These responses will be examined in terms of amplitude and latency of the brain responses (VEPs) as well as in terms of response topography. An estimation of the underlying intracranial sources of the VEPs will also be performed. The full analysis pipeline is referred to as ‘Electrical Neuroimaging’ as has been developed and validated by members of our team and their collaborators (eg, Michel and Murray, 2012; Murray et al., 2008; Brunet *et al*, 2011^52^). VEPs will be compared during (visit 1) and after (visit 2) pregnancy, as well as between women with and without GDM.

### Secondary outcomes

Secondary outcomes are weight, glycated haemoglobin (HbA1c), glucose measures at visits 1 and 2 (the latter only in women with GDM) and body composition (fat/lean mass). We will investigate eating rate, objectively using a novel eating recognition device (Auracle) and subjectively (reported perceived eating rate). Using validated self-report questionnaires, we will assess eating behaviours, including cravings (Food Craving Questionnaire-Trait-reduced), intuitive eating (ie,) (The French Intuitive Eating Scale-2 (IES-2)), external, emotional eating and cognitive restriction (The Three-Factor Eating Questionnaire). Depression scores will be assessed by Edinburgh Postnatal Depression Scale and current mood by PANAS questionnaire Positive and Negative Affective Schedule. Other measures will include self-reported stress level assessed with a questionnaire (The Perceived Stress Scale) and objectively measures of stress using Actiheart.

#### Data collection and visits

The study started in March 2022 and the end of the study is scheduled for June 2024.

The first visit will take place during pregnancy, at 24–36 weeks gestational age (visit 1) and the second visit at 6 months postpartum (visit 2).

After signing the informed consent, and before visit 1 and visit 2, participants will complete validated questionnaires online (see Questionnaires related to eating behaviour and mental health). They will be contacted by phone to complete missing data regarding their medical history as well as their lifestyle behaviours.

Before each visit, participants will be asked to eat a balanced meal around 12.00 hours (based on the Swiss Society for Nutrition recommendations; the patients are given examples and at the end will be checked what they eat) to minimise the bias of different satiety level, will come to the hospital at 13:30 hours and testing will be completed at 16 hours (table 1).

**Table 1 T1:** Study schedule

Flowchart of the study procedure	Visit 1	Visit 2
Study schedule		
Time point	3rd trimester of pregnancy	6 months post partum
Duration	Televisit: 10–30 min for medical history and 20–40 min for online questionnaires Visit: max 2 hours 30 min including breaks*	Televisit: 10–30 min for medical history and 20–40 min for online questionnaires Visit: max 2 hours 30 min including breaks*

Procedures and time				
Televisit before or after each of both of the physical visits (at home)				
Medical history if lacking in the chart and questions regarding lifestyle, by phone		10–30 min		
Questionnaires online: Food Craving Questionnaire-Trait-reduced, Edinburgh Postnatal Depression Scale, Edinburgh Handedness Inventory, TFEQ-R18, Intuitive Eating Scale-2		20–40 min	X	X
During the visit (in the EEG lab up to the break)				
Setup EEG, questionnaires: Perceived Stress Scale-10 Food Craving Questionnaire-State PANAS questionnaire: Positive and Negative Affective Schedule, current hunger level: Likert scale) + heart rate (Actiheart)	13:30–14:15 hours	30–45 min	X	X
Electroencephalography	14:15–15:10 hours	55 min	X	X
Break	15:10–15:20 hours	10 min	X	X
Bioimpedance and weight	15:20–15:30 hours	10 min	X	X
Positive and negative affective schedule current hunger level: Likert scale Break and Auracle* + questionnaire: Eating of the provided snacks and three questions regarding eating duration	15:30–15:45 hours	15 min	X	X
Height, blood pressure	15:45–15:50 hours	5 min	X	X
Capillary measure: glycated haemoglobin (HbA1c) Double check lunch composition	15:50–15:55 hours	5 min	X	X
Set-up glucose sensor: Freestyle Libre 1 (only for GDM) × 14 days	15:55–16:00 hours	5 min	X	X

*During the Auracle session, patients will eat different snacks that we provide.

EEG, electroencephalography; GDM, gestational diabetes mellitus; TFEQ-R18, Three-Factor Eating Questionnaire-Revised 18.

### Patient and public involvement

The development of the research question and outcome measures was also based on remarks from patients that were followed in clinical settings and we informally asked their advice while designing the study. Some results will be provided to participants at the end of their study as feedback by sending them to their healthcare providers. Interested patients will also receive an overall return of the results.

### Measures

#### Behavioural task/EEG

We will employ a behavioural task involving food pictures of variable fat and carbohydrate content and will record high-density VEPs (brain responses to visual stimuli via EEG) (figure 1). Using the Salzburg food picture database,^53^ we are going to show 4 blocks of 240 randomised images (200 pictures of food and 40 non-food objects together; 50 pictures of food and 10 non-food objects per block) to the participants. The food images are divided into four categories: HIGH-FAT/LOW-CARB; HIGH-FAT/HIGH-CARB; LOW-FAT/LOW-CARB; LOW-FAT/HIGH-CARB.

**Figure 1 F1:**
[figure not shown]
128-channel electroencephalography.

HIGH-FAT was defined by a fat content of >5 g/100 g (21.6±13.77 g/100 g) and LOW-FAT of <5 g/100 g (mean 1.1±1.29 g/100 g). Similarly, HIGH-CARB was defined as >15 g/100 g carb (48.57±21.13 g/100 g) and LOW-CARB as <15 g/100 g (4.59±4.59 g/100 g). We aimed for the contents to be as far as possible away from the cut-off to provide the best distinction.

Images will be identical in size, controlled for low-level visual features (like luminance) and will be presented on the computer monitor during EEG recording sessions. Immediately after the presentation of each image, women have to decide if the presented picture is a food or non-food object by pressing a button 1 or 2 on a response box. Accuracy and reaction time of behavioural responses will be collected. At the beginning of the experimental session, the participant will be presented with the instructions and will have to perform some trials (seven pictures of food and three of non-food) to familiarise herself with the task. Continuous 128-channel EEG will be recorded on the head surface. VEPs will be calculated separately for each image category (HIGH-FAT/LOW-CARB; HIGH-FAT/HIGH-CARB; LOW-FAT/LOW-CARB; LOW-FAT/HIGH-CARB). The preparation for the EEG recording will take approximately 30–45 min, while EEG sessions will last maximum 55 min. When the EEG experiment is completed, the patient will move to the preparation room for the validation task. Twenty pictures of food (five pictures from each food category) will be presented and the patient will be asked to rate how much she wants this food. During visit 2, four blocks with randomised images of food and non-food objects will be presented in a different order than during visit 1 to minimise potential sources of bias.

#### Heart rate and heart rate variability

During EEG and the Auracle testing, we will monitor the participant’s heart rate and heart rate variability to assess the level of arousal of the autonomic system. We will perform baseline and recovery measurements (2 min each) before and after EEG and the Auracle testing. For this purpose, we will use Actiheart, a compact chest-worn monitoring tool that apart from heart rate, measures inter beat interval. Specific time points before and after the test will be identified by a stopwatch. To analyse the data, we will use the commercial Actiheart Software and Kubios.

#### Body composition

Body composition will be measured by bioimpedance (BIA 101, Akern, Italy) at both visits. Using four electrodes (two on the right hand and two on the right foot, at a distance of 3–4 cm from each other) and low-voltage electric flows, we will measure the resistance (Rz) and reactance (Xc) of tissue to assess the fat and lean mass. We will also use BIA InBody s10 to measure body composition by bioimpedance at both visits. The body composition analysis of InBody S10 is derived from the four-compartment model, which include Total Body Water, Protein, Mineral and Body Fat.^54^

#### Eating behaviour (‘Auracle’) and choice of snacks

The Auracle (see figure 2) will be used as an objective measure of eating behaviour during snack session (see figure 3). Auracle is an eating-recognition system that measures vibrations generated from movement, chewing and teeth grinding. When worn, the contact microphone is positioned on the mastoid and when a person eats, vibrations from movement, chewing and grinding of teeth sensed by the device are transmitted and stored on an embedded memory card. This device automatically identifies the eating rate and rapidity as well as the duration of food intake and other related dynamics with an accuracy exceeding 92%.^55^ Auracle provides a holistic, detailed and accurate characterisation of objective correlates of eating behaviour. All of the sensors in Auracle (ADXL362 accelerometer and CM-01B microphone) are commercial, off-the-shelf devices. The device includes an MSP430 microcontroller (Texas Instruments, Dallas, Texas, USA), a push button and buzzer for user interaction. It is comfortable to wear because it is embedded in an elastic headband or a flexible plastic frame and possesses no risk to the mother or fetus. The Auracle device has been validated and has been used in healthy non-pregnant subjects.^55 56^

**Figure 2 F2:**
[figure not shown]
The Auracle: eating recognition system.

**Figure 3 F3:**
[figure not shown]
Eight snacks of different carbohydrate and fat content.

Eight different crunchy snacks of different carbohydrate and fat content (two of each corresponding to one of the four categories described in the EEG part) will be offered (figure 3). As eating behaviour will be measured with the ‘Auracle’ device, crunchy-textured snacks provide a stronger, more easily detected vibrational signal. Before the snack session, the patient will be asked the second time about their current level of hunger (1—not at all to 5—very hungry) and fill out the ‘PANAS’ questionnaire. The weight of the different snacks will be measured before and after the patient has finished eating to determine the number of kcal and the quantity of fat, protein and carbohydrates eaten. Furthermore, the time interval between the first and last bite will be also measured using the ‘Auracle’ device and a stopwatch. We will also ask the woman questions regarding her subjective perceived eating rate (perceived eating duration, perceived eating speed and current eating speed compared with usual eating speed).

#### Collection of blood samples

Capillary blood will be collected to measure HbA1c level. HbA1c will be analyzed by Afinion.

#### Glucose sensors

Women with GDM will use Freestyle Libre 1 glucose sensors (Abbott) for flash glucose measurement for 14 days. Sensors will be applied on the back of the arm, with a sterile fibre being inserted under the skin into the interstitial fluid. Patients use a dedicated application LibreLink and will have to scan the glucose sensor at least every 8 hours to transfer data. Data will be linked in a coded form to the online platform Libreview (https://www.libreview.com/). During pregnancy, results will be discussed with their healthcare provider during the visits. For the post partum visit, patients will receive feedback by phone.

#### Questionnaires related to eating behaviour and mental health

Women with and without GDM will fill out the same questionnaires during both visits (visits 1 and 2). Most women will fill out the questionnaires in French and a few in English, as around 80% of patients that participate in our studies are French-speaking. The following questionnaires will be filled out online before the study visits:

The French IES-2:^57^ Validated self-report questionnaire that assesses individuals’ tendency to follow their physical, hunger and satiety cues in determining when, what and how much to eat. The original version (English) consists of four subscales, Eating for Physical rather than Emotional Reasons (EPR, eight items), Reliance on Hunger and Satiety Cues (RHSC, six items), Unconditional Permission to Eat (UPE, six items) and the Body-Food Choice Congruence (three items) subscales. The validated French version, however, consists of 18 items divided into three subscales, the EPR (eight items), RHSC (six items) and the UPE (four items) subscales,^58^ and has also demonstrated good psychometric properties. In this study, we will assess intuitive eating with only the EPR and the RHSC subscales (14 items) of the French-adapted version of IES-2 and the English version. Scores of IES-2 range between 1 and 5. A higher score of the EPR subscale reflects eating as an answer to hunger and a lower score means eating to cope with emotional distress, whereas a higher score on the RHSC subscale signifies trust in internal cues, and a lower score reflects less ability to regulate food intake.

The Three-Factor Eating Questionnaire-Revised 18 (TFEQ-R18): Eighteen-item self-report questionnaire that measures three aspects of eating behaviours including cognitive restraint (six items), uncontrolled eating (nine items) and emotional eating (three items). Items are scored on a Likert scale ranging from 1 ‘almost always’ to 4 ‘never’. A short, revised version of the Stunkard and Messick TFEQ was developed by Karlsson *et al*.^59^ It has been also tested in the general population in France.^60^

Food Craving Questionnaire-Trait-reduced:^61^ Fifteen-item self-report questionnaire for the assessment of the frequency and intensity of food craving. It consists of five subscales: lack of control over eating (five items), thoughts or preoccupation with food (five items), intentions and plans to consume food (two items), emotions before or during food craving (two items) and cues that may trigger food craving (one item). Items are scored on a Likert scale from 1 ‘never/not applicable’ to 6 ‘always’. Higher scores reflect food-cue elicited craving. The French version was validated and has shown good psychometric proprieties.^62^

Edinburgh Postnatal Depression Scale (EPDS):^63^ Ten-item self-report questionnaire to examine postnatal depression symptoms over the previous week, which are scored on a 4-point Likert scale. Scores range from 0 to 30. Higher scores indicate a higher risk of postnatal depression. The French version of the EPDS demonstrated good psychometric properties.^64^

Edinburgh Handedness Inventory short form:^65^ This short (four items) and simple questionnaire measures the preference to use one hand more than the other. The French version has been previously used in research.^66^

During the study visits, participants will complete the following questionnaires:

The Positive and Negative Affective Schedule questionnaire (PANAS):^67^ Self-report questionnaire that assesses mood or emotion during the last month. It consists of 20 items, 10 items measuring positive affect (eg, enthusiastic, proud) and 10 items measuring negative affect (eg, scared, ashamed), which are scored on a Likert scale from 1 ‘not at all’ to 5 ‘extremely’. Individual scores on the PANAS range from 10 to 50, with higher scores representing higher levels of positive affect. The validated French version has shown good psychometrics.^68^

The Perceived Stress Scale (PSS-10): Ten-item questionnaire widely used to assess stress levels during the last month. Responses are rated on a Likert scale from 0 ‘never’ to 5 ‘very often’. The results range from 0 to 40, with higher scores indicating higher perceived stress. The French version of PSS-10 has shown good psychometric properties.^69^

The Food Craving Questionnaire-State:^70^ Fifteen-item questionnaire measures the intensity of momentary food cravings. Items are scored on a 5-point scale ranging from ‘strongly disagree’ to ‘strongly agree’. Higher scores indicate more intense current food cravings. The French version was translated and used in previous research by the research team of our collaborator [name].^66^

The current hunger level scale: This is one item developed for this study assessing the current perceived hunger level using a Likert scale ranging from 1 ‘just a little/not at all’ to 5 ‘very much’.

The food wanting questionnaire: Twenty-item questionnaire was developed for this study and will be completed after the EEG (see Behavioural task/EEG). Women will be shown 20 pictures of food and asked ‘How much do you want this food?’. They will then have to indicate their response on a Likert scale from 0 ‘not at all’ to 10 ‘very much’.

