**Methods and analysis:**

This prospective observational study will include 20 women with and 20 without GDM, that have valid data for the primary outcomes. Data will be assessed at 24–36 weeks gestational age and at 6 months post partum. The primary outcomes are brain responses to food pictures of varying carbohydrate and fat content during pregnancy and in the post partum using electroencephalography. Secondary outcomes including depressive symptoms, current mood and eating behaviours will be assessed with questionnaires, objective eating behaviours will be measured using Auracle and stress will be measured with heart rate and heart rate variability (Actiheart). Other secondary outcome measures include body composition and glycaemic control parameters.

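### The PANAS is described as a last-month measure but used as the current-mood measure twice within one visit, and its one stated scoring direction cannot apply to the negative-affect items

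*Protocol article*

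**What the plan says.** All references are to the protocol article.

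- **Construct.** The abstract (Methods and analysis) states: "Secondary outcomes including depressive symptoms, current mood and eating behaviours will be assessed with questionnaires". The Secondary outcomes section assigns the instrument: "current mood by PANAS questionnaire Positive and Negative Affective Schedule".
- **Timing.** Table 1 (Data collection and visits) lists the scale in the EEG set-up slot, 13:30 to 14:15: "PANAS questionnaire: Positive and Negative Affective Schedule, current hunger level: Likert scale) + heart rate (Actiheart". It lists it again in the 15:30 to 15:45 slot: "Positive and negative affective schedule current hunger level: Likert scale Break and Auracle". The section on the Auracle and the choice of snacks confirms the repeat. It says "Before the snack session, the patient will be asked the second time about their current level of hunger" and has the PANAS filled out at the same point.
- **Reference period.** The section on questionnaires describes the PANAS as a "Self-report questionnaire that assesses mood or emotion during the last month".
- **Scoring.** The same entry says "It consists of 20 items, 10 items measuring positive affect (eg, enthusiastic, proud) and 10 items measuring negative affect", each rated 1 to 5. It then gives one rule: "Individual scores on the PANAS range from 10 to 50, with higher scores representing higher levels of positive affect".
- **Purpose.** Objective 3 relates brain responses to emotional states and stress levels. The hypothesis at the end of the Introduction names negative emotions as a possible influence on brain responses and on eating.

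**The concern.** The reference period and the use of the scale do not agree. A current-mood measure placed immediately before the EEG, and again immediately before eating, makes sense only if it asks about the moment. If women are asked about the past month, both administrations in a visit ask nearly the same question, and neither gives mood at the time of the task. The analysis of emotional state would then rest on past-month affect under a current-mood label.

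The scoring sentence adds a second difficulty. The hypothesis concerns negative emotion, yet the only direction stated is for positive affect. A reader who follows the text has no correct rule for the ten negative items.

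**Working it through.** **Step 1: reproduce the stated score range.** Inputs from the questionnaire section: 20 items, 10 positive and 10 negative, each rated 1 to 5.

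| Score | Minimum | Maximum |
|---|---|---|
| One 10-item subscale | 10 × 1 = 10 | 10 × 5 = 50 |
| All 20 items summed | 20 × 1 = 20 | 20 × 5 = 100 |
| Positive minus negative | 10 − 50 = −40 | 50 − 10 = 40 |

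Of these, only a single 10-item subscale gives the stated 10 to 50. With the stated direction, the sentence describes the positive-affect subscale. The negative subscale also runs from 10 to 50, but a higher value there means more negative affect, so the sentence cannot hold for it. No other sentence gives the negative score or its direction.

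**Step 2: time between the two administrations.** Inputs from Table 1: first slot 13:30 to 14:15, second slot 15:30 to 15:45.

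- Shortest gap: 14:15 to 15:30 = 75 minutes.
- Longest gap: 13:30 to 15:45 = 135 minutes.

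**Step 3: overlap of two one-month windows.** Taking a month as 30 days (an assumption), the window is 30 × 24 × 60 = 43,200 minutes. The part not shared is 75/43,200 = 0.17% to 135/43,200 = 0.31%. At least 99.7% of the recall period is common to both administrations, so a last-month form has almost no room to register a change in mood between the EEG and the snacks.

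**Step 4: is the reference period settled elsewhere?** The article states reference periods with some care for other scales: the previous week for the EPDS, the last month for the PSS-10, and momentary craving for the state version of the Food Craving Questionnaire as distinct from the trait version. The PANAS entry is therefore a specific statement, and it conflicts with the abstract, the Secondary outcomes section and Table 1. No sentence gives a momentary instruction for the PANAS.

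**Step 5: can another measure stand in?** The EPDS covers the previous week and the PSS-10 the last month. Actiheart records heart rate and heart rate variability during the EEG and the Auracle session, which reflects autonomic arousal but does not tell positive from negative emotion. The PANAS is the only scale that the article names for current mood.

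**The case against.** The strongest reply is that this may be a slip in describing the instrument. The article does not reproduce the form. The abstract, the Secondary outcomes section and the pairing with current-hunger ratings all point to a momentary instruction, and the next entry, for the PSS-10, also refers to the last month, so carried-over wording is plausible. This stands as far as it goes. A reader might infer that emotional state is in fact being mismeasured; the document does not show that. It shows a contradiction that only the form can settle.

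On scoring, a reader might infer that every negative-affect association will come out with the wrong sign. That would require the team to read the negative items as positive affect, which nothing in the article says. It separates the two sets of items, and the stated range fits the positive subscale. The negative items are collected and can still be scored correctly. What remains is that the sentence is presented as covering the PANAS as a whole and is wrong for half of it.

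It is also fair to say that the article plans no analysis of within-visit mood change, and that the choice of which administration enters which model can be left to a statistical analysis plan. Neither point removes the conflict: even a single pre-EEG score has a different meaning under the two reference periods. Nor could an analysis plan change the instruction under which answers were already given.

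**Conclusion.** The contradiction over the reference period is explicit and unresolved. If the last-month description is what the women see, the scale gives past-month affect. That could still be compared between women and between visits, but it would not be mood at the EEG or before the snacks. The scoring rule is correct for positive affect only.

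Severity is moderate. The PANAS is a secondary outcome and all analyses are declared exploratory. Heart rate measures, the PSS-10 and the EPDS also bear on stress and emotion, though none replaces a momentary affect score. The primary EEG outcomes, the sample size and the group comparison are untouched. The conclusion rests on the text alone; the instruction on the form in use is unknown.

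**What to change.** 1. Check the instruction printed on the PANAS form used so far, in both the French and the English versions.
2. If it is momentary, correct the instrument description so that it agrees with the current-mood outcome and with the two administrations per visit.
3. If it says last month, move to a momentary (right now) instruction at both administrations. Report the data already collected as past-month affect, and do not pool them with momentary data. Recruitment began in March 2022, so a mid-study change could leave one woman with different reference periods at her two visits. Record the instruction used for each administration.
4. Replace the scoring sentence with two: positive affect 10 to 50, higher meaning more positive affect; negative affect 10 to 50, higher meaning more negative affect.

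The cost is a check of the form and a few lines of text, plus separate labelling of earlier data, with fewer comparable observations, if the last-month wording was used. Sample size, visits and procedures do not change.
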